## 1. KEY STUDY ELEMENTS

### 1.1. Synopsis

|                                 |                                                                                                                                                                                                                                                                                                                                                                                                                                                                                                                                                                                                                                                                                                                                                                                                                                           |
|---------------------------------|-------------------------------------------------------------------------------------------------------------------------------------------------------------------------------------------------------------------------------------------------------------------------------------------------------------------------------------------------------------------------------------------------------------------------------------------------------------------------------------------------------------------------------------------------------------------------------------------------------------------------------------------------------------------------------------------------------------------------------------------------------------------------------------------------------------------------------------------|
| Tracking number:                | CN-SMG-11774                                                                                                                                                                                                                                                                                                                                                                                                                                                                                                                                                                                                                                                                                                                                                                                                                              |
| Protocol Title:                 | Pediatric Patients with Spinal Muscular Atrophy in China:
A Nationwide Registry                                                                                                                                                                                                                                                                                                                                                                                                                                                                                                                                                                                                                                                                                                                                                        |
| Version Number:                 | 2.0                                                                                                                                                                                                                                                                                                                                                                                                                                                                                                                                                                                                                                                                                                                                                                                                                                       |
| Phase of Development:           | N/A                                                                                                                                                                                                                                                                                                                                                                                                                                                                                                                                                                                                                                                                                                                                                                                                                                       |
| Study Indication:               | Spinal Muscular Atrophy (SMA)                                                                                                                                                                                                                                                                                                                                                                                                                                                                                                                                                                                                                                                                                                                                                                                                             |
| Study Rationale:                | 
The planned registry project will provide a platform to collect longitudinal clinical routine data on Chinese SMA patients. Items for data collection will be aligned with TREAT-NMD. SMA has a broad spectrum of severity and clinical trials only cover a subgroup of these. Therefore there is a strong need to monitor the clinical status of all treated and untreated SMA in China. The registry will facilitate the understanding of disease progression and treatment effectiveness for Chinese pediatric patients diagnosed with SMA.
                                                                                                                                                                                                                                                                                     |
| Study Objectives and Endpoints: | 
The primary objective of the study is to describe the natural history and utilization of DMT among pediatric Chinese patients with 5q-SMA.
 
The primary endpoints that relate to this objective are not applicable.
 
Additional objectives and endpoints are as follows:
 

• To describe the effectiveness of disease modifying therapy (DMT)

○ Time to mortality, motor function, motor measures, pulmonary function, scoliosis, hospitalizations and comorbidities, clinical observations, patient reported outcomes, wheelchair use, nutrition and electrophysiology and biomarkers

• To describe the safety of DMT

○ Adverse events and serious adverse events

 |
| Study Design:                   | This is a multicenter registry study that will examine SMA natural history and DMT outcomes in a real-world setting                                                                                                                                                                                                                                                                                                                                                                                                                                                                                                                                                                                                                                                                                                                       |

CONFIDENTIAL

The information contained herein may not be used, disclosed, or published without the written consent of  
Biogen

|                             |                                                                                                                                                                                                                                                                                                                                                                                                                                                                                                                                                                                                                                                                                                               |
|-----------------------------|---------------------------------------------------------------------------------------------------------------------------------------------------------------------------------------------------------------------------------------------------------------------------------------------------------------------------------------------------------------------------------------------------------------------------------------------------------------------------------------------------------------------------------------------------------------------------------------------------------------------------------------------------------------------------------------------------------------|
|                             | both prospectively and retrospectively. Patients will be observed based on regular prescription and visit schedules.                                                                                                                                                                                                                                                                                                                                                                                                                                                                                                                                                                                          |
| Study Location:             | Approximately 20 to 25 sites in China are planned.                                                                                                                                                                                                                                                                                                                                                                                                                                                                                                                                                                                                                                                            |
| Study Population:           | Pediatric SMA patient in China.
Detailed criteria are described in Section 6.1 and 6.2.                                                                                                                                                                                                                                                                                                                                                                                                                                                                                                                                                                                                                    |
| Number of Planned Patients: | Approximately 600 patients will be enrolled.                                                                                                                                                                                                                                                                                                                                                                                                                                                                                                                                                                                                                                                                  |
| Treatment Supply            | Nusinersen will not be supplied for this study. The study will observe patients who have been prescribed DMT treatments by their physician (Investigator) according to the local Prescribing Information.                                                                                                                                                                                                                                                                                                                                                                                                                                                                                                     |
| Visit Schedule:             | The data collected at enrollment will coincide with a routine clinical visit to the Investigator. Subsequent data will also be collected during routine clinical visits for up to 60 months from enrollment. For patients who received nusinersen, visits of the first four loading doses are anticipated to occur on day 0, day 14, on day 28, and on day 63 and the following maintenance doses are anticipated to occur at approximately every 4 months. Among untreated patients or those treated with other DMTs, first three visits are anticipated to occur on day 0, day 90 and on day 180, and then occurring at approximately every 6 months. Visits may vary according to local standards of care. |
| Risk-Benefit Analysis:      | No additional risks will be imposed on participants other than the existing risks present with the treatment or the disease, because the study will only observe regular clinical practice.                                                                                                                                                                                                                                                                                                                                                                                                                                                                                                                   |

CONFIDENTIAL

The information contained herein may not be used, disclosed, or published without the written consent of  
Biogen

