## 1.2. Study Design Schematic

[figure not shown]

**Figure 1.** Diagram of the registry design for data collection

Note:

1. The study will retrospectively collect available data for patients who initiated DMT prior to recruitment initiation starting from index date. Index date will not be earlier than April 28th, 2019, which was the launch date of nusinersen, the first DMT in China. Baseline data will be collected within 30 days prior to the index date.
2. The index date for patients treated with any DMTs will be the date of DMT initiation, and the index date for those untreated patients will be the date of study enrollment.

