## 1.3. Recommended Schedule of Activities

Visit schedules for the group of SMA patients treated with DMT (including nusinersen and other DMTs) and the group of untreated patients will be described in Table 1. Data for the registry will only be collected within regular SMA patient visits.

CONFIDENTIAL

The information contained herein may not be used, disclosed, or published without the written consent of  
Biogen

Table 1. Expected Tests and Assessments

| Tests and Assessments                                            | Enrollment data collection points | Follow-up data collection points
For nusinersen-treated patients, it is expected they will be observed on days 14, 28, and 63 and every 4 months thereafter.
For untreated patients or those on other DMTs, it is expected they will be observed on days 90a and 180 and every 6 months thereafter. |
|------------------------------------------------------------------|-----------------------------------|------------------------------------------------------------------------------------------------------------------------------------------------------------------------------------------------------------------------------------------------------------------------------------------------------------------------------------|
|                                                                  | V0                                | V1-V17                                                                                                                                                                                                                                                                                                                             |
| Informed Consent                                                 | X                                 |                                                                                                                                                                                                                                                                                                                                    |

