#### 4. STUDY OBJECTIVES AND ENDPOINTS

The objective of this registry is to longitudinally follow up pediatric patients (aged <18) with 5q-SMA to obtain information on both the natural history of the disease (from patients who received supportive care only) and the effectiveness and safety of disease modifying therapies (DMT), nusinersen in particular. Disease characteristics, treatment patterns, and outcomes (please refer to the section of outcome measurements) will be collected by extracting relevant information from medical records. Since this is not an experimental study, treatment plans will not be altered by participation, and all clinical managements including supportive care, DMTs, and concomitant medications will be administered based on healthcare providers' clinical judgements without stakeholders' interventions.

Currently, three DMT drugs are available including nusinersen, onasemnogene abeparvovec, and risdiplam in the US, but only nusinersen is approved by the National Medical Products Administration (NMPA) in China. In line with the main objective of this registry, and in case there will be more NMPA-approval DMTs in the future, in addition to nusinersen, this registry will also collect information on other DMTs once they become available in China.

| Primary Objective                                                                                    | Primary Endpoints                                                                                                                                                                                                                       |
|------------------------------------------------------------------------------------------------------|-----------------------------------------------------------------------------------------------------------------------------------------------------------------------------------------------------------------------------------------|
| To describe the natural history and utilization of DMT among pediatric Chinese patients with 5q-SMA. | Not applicable.                                                                                                                                                                                                                         |

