### **6.3. Screening**

Once informed consent is obtained, a unique identification number is assigned that will be used on study-related documents pertaining to the participant. Any identification numbers that are assigned will not be reused even if the participant does not continue in the study. Study sites are required to document all screened participants initially considered for inclusion in the study.

CONFIDENTIAL

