This registry study will include both retrospective and prospective data collection. Eligible SMA patients will be recruited during the 24-month recruitment period and will be prospectively followed up to the end of study or deaths or willing to drop out, whichever comes first. If patients received DMT (including nusinersen and other DMTs) prior to the recruitment initiation and post April 28th, 2019 (as the date the first DMT, nusinersen, was launched in Chinese market), data will be retrospectively collected via medical chart review. Retrospective data collection will be considered complete for a participating patient if data of last available medical chart or latest survival status before recruitment initiation have been recorded in the electronic case report form (eCRF). Otherwise, patients will be prospectively followed up to the end of study or deaths or willing to drop-out, whichever comes first, after signing the ICF. For the DMTs treated group, the date of patients initiating DMT will be defined as the index date. For patients not receiving DMTs, the date of enrollment into the registry will be the index date. Baseline data will be collected within 30 days prior to the index date. Diagram of data collection is provided in Figure 1.

Since this is a non-interventional study and does not impose a visit schedule, patients will be treated according to physician's decisions. Only data that are available during routine visits will be documented. Recommended data collection schedules are set up to reflect the most likely patterns of routine clinical care of patients with and without DMT. To ensure the excellent level of compliance on data collection, schedule points are set to follow clinical routine visits, most likely happen on day 0, 14, 28, 63 then every 4 months for patients treated with nusinersen, and at day 0, 90 (in children with SMA type 1 < 2 years of age), 180 then every 6 months for untreated patients or those on other DMT. Retrospective data will be extracted according to the schedule as well.

CONFIDENTIAL

All data collected within the registry will be entered to the registry-specific e-forms by the responsible investigator, or a designated person, as timely as possible. Data entry and data corrections on e-forms are automatically tracked in the audit trail created by the EDC system. The EDC system and related IT infrastructure of this project will be based inside China.

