### **12.4. Participant Information and Consent**

Prior to any data collection under this protocol, informed consent with the approved ICF must be obtained in accordance with local practice and regulations.

The background of the proposed study, the procedures, the benefits and risks of the study, and that study participation is voluntary for the participant must be explained to the participant (or the participant's legally authorized representative). The participant must be given sufficient time to consider whether to participate in the study.

In addition, participants who have the capacity should provide their assent to participate in the study. The level of information provided to participants should match their level of understanding as determined by the Investigator and in accordance with applicable regulations and guidelines.

A copy of the signed and dated ICF and assent must be given to the participant and/or the participant's legally authorized representative. The original signed and dated ICF will be retained with the study records. Local regulations must be complied with in respect to the final disposition of the original and copies of the signed and dated ICFs.

Confirmation of informed consent and assent must also be documented in the participant's medical record.

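### Children who started a DMT before enrolment, then stopped and left care, are likely to be under-represented, so describing everyone from the index date tends to understate discontinuation

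*Protocol*

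**What the plan says.** **Time zero.** Section 1.2 states that "The index date for patients treated with any DMTs will be the date of DMT initiation", and Section 9 repeats it: "For the DMTs treated group, the date of patients initiating DMT will be defined as the index date". The earliest permitted index date is 28 April 2019. For children who began a DMT before recruitment opened, the course since then is filled in from charts.

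**Entry.** Section 11.4 schedules the first enrolment for Q3 2021, and Section 9 gives 24 months of recruitment. The Synopsis (Visit Schedule) says "The data collected at enrollment will coincide with a routine clinical visit to the Investigator". Section 1.3 adds "Data for the registry will only be collected within regular SMA patient visits". Section 12.4 says "Prior to any data collection under this protocol, informed consent with the approved ICF must be obtained in accordance with local practice and regulations", and no waiver for chart-only patients is stated.

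**Expected contact.** For children on nusinersen after loading, "the following maintenance doses are anticipated to occur at approximately every 4 months". Untreated children and those on other DMTs are expected about every 6 months once past the first visits.

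**Objectives.** The primary objective in Section 4 is "To describe the natural history and utilization of DMT among pediatric Chinese patients with 5q-SMA". Adverse events and serious adverse events are endpoints of an additional objective.

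**Safeguards.** Section 9 asks physicians to enrol eligible patients consecutively, in order to avoid selection bias. Section 6.3 says "Study sites are required to document all screened participants initially considered for inclusion in the study".

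**Analysis.** Section 11.2 makes all patients the default set and permits subgroup repeats. Section 11.3 uses Kaplan-Meier for time-to-event endpoints and leaves details to the SAP.

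**The concern.** A prior starter's history is counted from DMT start, but the child comes into view only later, through a visit and a signed consent. Between the two dates some children will have stopped. Those who stopped and drifted away from the centre are less likely to be enrolled than those who stayed on treatment and keep coming for doses. This is left truncation with selection on attendance, and attendance is linked to the very thing being described.

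Neither stated safeguard reaches these children. Consecutive inclusion covers those who present. The screening record covers those who were considered. Neither gives a count of eligible starters who had already left when the site opened, and no later analysis can recover a count that was never collected.

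At stake are the discontinuation and switching figures, which are a natural part of describing utilization, and the frequency of adverse events that led to stopping. Children who start a DMT at or after enrolment are not affected, but a single description of all patients carries the distortion into the overall figure.

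**Working it through.** The protocol has no sample size calculation and states no persistence or discontinuation rate, so there is no figure of its own to reproduce. The check has three parts.

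**1. How long the unobserved gap can be (protocol dates).**
- 28 April 2019 to 1 July 2021: 26.1 months. To 30 September 2021: 29.1 months.
- Adding 24 months of recruitment: 50.1 to 53.1 months. This is the extreme; a child attending regularly would normally be enrolled soon after the site opens.

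**2. Effect on a simple discontinuation share (assumed inputs).** Let d be the true share of prior starters who stopped before enrolment, and r the chance that a stopper is enrolled relative to a continuer. Neither is in the protocol.

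Observed share = d·r / (d·r + 1 − d)

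| d | r = 0.75 | r = 0.5 | r = 0.25 |
|---|---|---|---|
| 20% | 0.15/0.95 = 15.8% | 0.10/0.90 = 11.1% | 0.05/0.85 = 5.9% |
| 30% | 0.225/0.925 = 24.3% | 0.15/0.85 = 17.6% | 0.075/0.775 = 9.7% |

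With r = 1 the observed share equals d and there is no bias. With any r below 1 the share is too low.

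**3. Effect on a Kaplan-Meier curve of time on treatment (simulation, assumed inputs).** Each scenario has 60,000 starters. Starts are uniform over the 27.5 months before recruitment (about the middle of 26.1 to 29.1), and every enrolled child enters at recruitment start. The stopping hazard is constant, −ln(1 − a)/12 per month for annual stopping a. A share q of those who stop before recruitment leave and are never enrolled. If all continuers enrol, r = 1 − q.

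12-month persistence, counted from DMT start:

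| True | q = 0 | q = 25% | q = 50% | q = 100% |
|---|---|---|---|---|
| 95% | 94.9% | 96.0% | 96.8% | 98.8% |
| 90% | 90.0% | 91.5% | 93.6% | 97.6% |
| 80% | 80.1% | 83.1% | 86.5% | 94.6% |

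For q of 25% to 100%, the overstatement runs from 96.0 − 95 = 1.0 to 94.6 − 80 = 14.6 percentage points. The share of starters missing from the registry runs from 1.4% to 21.8%.

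Counting the children still on treatment as at risk only from enrolment gives 94.5–95.2%, 89.3–89.9% and 79.6–81.6% for true values of 95%, 90% and 80%. Delayed entry therefore recovers the truth to within simulation error. In this set-up the entry time is unrelated to the risk of stopping, and the recovery depends on that. Delayed entry applies to time on treatment. It does not repair a simple proportion who stopped, or who had an adverse event, among prior starters.

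**The case against.** The strongest reply is that the protocol does not shut these children out. A reader might infer that a child who stopped and left has no chance of entry, and the documents do not go that far. The sentence tying enrolment data to a visit says when data are taken; it is not an eligibility rule. Section 6.1 asks for consent, genetic confirmation and age under 18, not current attendance or current treatment. Section 9 treats retrospective collection as finished once the final chart entry or survival information before recruitment is in the eCRF, which may hint at chart-only records. Section 10.3.2 also foresees serious events found through secondary use of data. This stands as a limit on the claim. It does not remove it: the Section 9 sentence concerns patients who are already participating, and nothing there lifts the visit rule of Section 1.3 or the consent rule of Section 12.4. The position is unclear rather than closed.

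Second, stopping is not leaving. Section 3.1 takes patients whatever their regimen. At visits about every 6 months, a stopper who still attends has roughly 24/6 = 4 chances of enrolment during recruitment. This also stands, and it confines the bias to children who both stopped and left.

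Third, a reader might take tolerability to be part of the primary objective. It is not: adverse events belong to an additional objective, and persistence is not named anywhere as an endpoint.

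Fourth, subgroup displays and delayed entry are matters a protocol may leave to the SAP, which is not shown. That is fair for the analysis detail. The entry rule, the index date, the all-patients default and the content of the screening log are fixed in the protocol.

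**Conclusion.** The point holds in a limited form. Among children who started a DMT before enrolment, those who stopped and no longer attend are likely to be under-represented. Describing all patients together from the index date would then tend to understate discontinuation, switching and adverse events that led to stopping. The direction follows whenever stoppers are enrolled less often than continuers.

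The size cannot be settled from the protocol. With 20% truly stopping and relative enrolment of 0.25 to 0.75, the observed share would be 5.9% to 15.8%. With assumed annual stopping of 5% to 20% and 25% to 100% of stoppers leaving, 12-month persistence would look about 1 to 15 points too high. All of these inputs are assumptions.

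One might go further and conclude that the main utilization summary must be restricted to children who start at or after enrolment. The documents do not compel that. It gives up precision and discards much of what the retrospective part was built to collect, and separate display beside the overall figure exposes the problem at lower cost. For a descriptive registry this is a foreseeable bias that is worth reducing and reporting, not a flaw that invalidates the design.

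**What to change.** 1. **Reconcile the entry wording.** Bring Section 9 into line with the Synopsis (Visit Schedule) and Sections 1.3 and 12.4, so that it is clear whether prior starters who no longer attend can be included from charts and, if so, under what consent arrangement.
2. **Separate the groups in Section 11.** Show utilization and adverse event summaries for children already treated at enrolment and for those starting at or after enrolment, beside the overall figure. In Kaplan-Meier analyses of time on treatment, count prior starters as at risk only from enrolment, and state the assumption that entry timing is unrelated to the risk of stopping. Children who had already stopped by enrolment add no time at risk to that curve and should be described alongside it.
3. **Count those missed.** Extend the Section 6.3 log so that each site reports, as far as ethics approval allows, how many eligible children it has started on a DMT since 28 April 2019, split into enrolled, attending but not enrolled, and no longer attending. The share missed can then be reported with the results.

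The cost is wording in the protocol and SAP, one extra count table per site, and wider intervals in the separate groups. No visit, treatment or clinical rule changes.
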